## Abstract

**Introduction:**

Microwave imaging presents several potential advantages including its non-ionising and harmless nature. This open, multicentric, interventional, prospective, non-randomised trial aims to validate MammoWave’s artificial intelligence (AI)-based classification algorithm, leveraging microwave imaging, to achieve a sensitivity exceeding 75% and a specificity exceeding 90% in breast screening.

**Methods and analysis:**

10 000 volunteers undergoing regular mammographic breast cancer screening will be recruited across 9 European centres and invited to participate in the clinical study, involving MammoWave testing on both breasts. MammoWave results will be checked against the reference standard, to be intended as the output of conventional breast examination path (with histological confirmation of cancer cases) with 2 years follow-up. Anonymised clinical and MammoWave’s results, including microwave images, associated features and a label provided by the AI-based classification algorithm, will be collected and stored in a dedicated electronic case report form. The prospective study will involve a comparative analysis between the output of the conventional breast examination path (control intervention) and the labels provided by MammoWave’s AI system (experimental intervention). These labels will categorise breasts into two groups: breast With Suspicious Finding, indicating the presence of a suspicious lesion or No Suspicious Finding, indicating the absence of a lesion or the presence of a low-suspicion lesion. This trial aims to provide evidence regarding the novel MammoWave’s AI system for detecting breast cancer in asymptomatic populations during screening.

**Ethics and dissemination:**

This study was approved by the Research Ethics Committee of the Liguria Region (CET), Italy (CET-Liguria: 524/2023—DB id 13399), the Research Ethics Committee of Complejo Hospitalario de Toledo (CEIC), Spain (CEIC-1094), the National Ethics Committee for Clinical Research (CEIC), Portugal (CEIC-2311KC814), the Bioethical Committee of Pomeranian Medical University in Szczecin, Poland (KB-006/23/2024) and the Zurich Cantonal Ethics Commission, Switzerland (BASEC 2023-D0101). The findings of this study will be disseminated through academic and scientific conferences as well as peer-reviewed journals.

**Trial registration number:**

NCT06291896.

STRENGTHS AND LIMITATIONS OF THIS STUDYThis is the first multicentric, prospective study to evaluate the sensitivity and specificity of MammoWave’s artificial intelligence (AI) solution within the framework of an asymptomatic population-based programme for breast cancer detection.The MammoWave device will use an AI-powered clinical decision support system to automatically provide radiologists with a dedicated label indicating the presence or absence of suspicious findings in each breast.As a reference standard, the 2-year follow-up with histological confirmation of cancer cases will be used.Study limitations include its non-randomised design.The axillary region of the breast is not captured within MammoWave’s cup.

## Introduction

 Breast cancer (BC) stands as the most prevalent cancer among women globally, with one in eight women experiencing its impact in their lifetime, rendering it a paramount challenge in public health.^1^,^3^ In response, many countries have instituted national or regional programmes dedicated to early detection, exemplified by screening campaigns aimed at mitigating the burden of BC.^4 5^ At the European level, the European Commission has always been committed to the fight against cancer, stimulating various initiatives such as the Europe’s Beating Cancer Plan and the Mission Cancer, and acting by developing evidence-based recommendations. In fact, the European Commission Initiative on Breast Cancer (ECIBC) regularly updates a list of guidelines to perform and optimise breast screening practices, according to the existing level of evidence in used imaging technologies, age of screening and frequency.^6^,^8^

Full-field digital mammography (DM), also called simply DM and digital breast tomosynthesis (DBT) serve as the gold standard technologies for mammographic screening, having demonstrated efficacy in reducing BC mortality through randomised controlled trials.^59^,^12^ However, these imaging modalities are not without limitations and potential adverse effects, including ionising radiation exposure, breast compression discomfort and inherent performance constraints associated with X-ray-based methods. Notably, dense breast tissue can diminish mammographic sensitivity, leading to reduced detection rates and increased rates of false positives. To mitigate these challenges, recommendations such as double reading by expert radiologists and optimising screening age and frequency have been proposed, considering the risk–benefit ratio of mammography.^7 8 13^ Indeed, risks associated with X-rays’ cumulative effect and low sensitivity in dense breasts, which may be reduced to 57.8%,^14^ limit the use of mammography in younger women or in reduced time intervals. In general, women are eligible for biennial screening only after the age of 45 according to ECIBC; nevertheless, recent studies estimate that 32.4% of new cancers in women aged under 50 are BCs.^3 15^ Moreover, emerging technologies such as Computer Aided Detection systems, based on deep learning algorithms (artificial intelligence, AI), are aiding radiologists in interpretation and decision-making processes, offering potential improvements in screening efficacy.^16^,^22^

Recognising the imperative of early detection, attention has turned towards novel technologies such as microwave breast imaging (MBI) as a promising avenue for overcoming the limitations of conventional X-ray-based approaches. MBI operates without ionising radiation, using radiofrequency (RF) signals to discern between healthy and malignant breast tissues based on their dielectric properties.^23^ Malignant cells, characterised by higher water and sodium accumulation, exhibit distinctive dielectric properties (conductivity and permittivity), allowing for microwave discrimination and cancer detection.^24^ Various MBI prototypes have been developed and clinically tested, among which MammoWave (UBT—Umbria Bioengineering Technologies Srl, Italy) has garnered attention. MammoWave employs low-power microwaves and has demonstrated promising sensitivity for breast lesion detection in previous clinical trials,^25^,^33^ offering a non-compressive and safe imaging alternative that may be suitable for population-based mass BC screening.

Here, we introduce the approved clinical protocol (full title: A Clinical Investigation to Evaluate Microwave Imaging Via MammoWave in a Population-based Screening Program for Early Breast Cancer Detection, v. 1.0 of 04/09/2023) for an open, multicentric, interventional, prospective and non-randomised trial aimed at evaluating, for the first time, MBI via MammoWave within the context of population-based BC screening. The study has been activated in the framework of the European cofunded project MammoScreen (‘Innovative and safe microwave-based imaging technology to make BC screening more accurate, inclusive and female-friendly’), under the programme Horizon Europe 2021–2027, grant ID 101097079. UBT is the sponsor of the study. Potential advantages and current limitations of MammoWave’s solution are reported in box 1.

Box 1Use of Mammowave’s artificial intelligence (AI) solution in breast screening: advantages and limitationsAdvantagesMammoWave’s solution is based on harmless, non-ionising microwave imaging which may allow more frequent examinations with no age restrictions.Dedicated facilities and sophisticated settings are not necessary.The scanning protocol, lasting 8 min per breast, is simple: a technician will help the patient lie down, introducing the breast in a dedicated cup. Then, microwave images are reconstructed on an external server, and an AI-powered algorithm (machine learning approach) provides a label for each breast.MammoWave’s AI is operator-free (no image interpretation is required).LimitationsCurrently, there are no guidelines including the use of microwave imaging technologies in clinical practice.The cost-effectiveness and impact of implementing microwave imaging technologies have not been approached.The impact of hormonal changes in scattered radiofrequency signals and corresponding MammoWave microwave images during a woman’s lifetime or menstrual cycle should be investigated.

## Methods and analysis

### MammoWave device and imaging algorithm

MammoWave (figure 1) is a new breast imaging device using safe, non-ionising low-power microwaves (RF signals), akin to those in mobile communications. It consists of two antennas emitting low-power (<1 mW) RF signals in the microwave band (1–9 GHz) to illuminate the breast and measure corresponding scattered electromagnetic fields (denoted as S_21_). The device’s hardware comprises a cylindrical aluminium hub internally coated with an absorption cone structure, creating an anechoic chamber to absorb reflections of electromagnetic waves that could cause noise/artefacts during data acquisition. Two motorised arms support both antennas, rotating around the azimuth to irradiate the breast and capture scattered electromagnetic fields. Both transmitting (TX) and receiving (RX) antennas are connected to a vector network analyser (VNA) for precise signal transmission and measurement. The acquisition configuration involves 10 TX positions grouped into 5 doublet sections with centres at 0°, 72°, 144°, 216° and 288°, with the RX antenna collecting signals at 80 positions around the breast for each TX position. The VNA acquires the S_21_ parameter for 1601 frequencies from 1 to 9 GHz, in 5 MHz increments. A programming logic controller inside the hub controls all components, providing shield from external interferences and structural support. The examination bed, atop the hub, includes a plexiglass cup to accommodate the volunteer’s breast without compression, with various cup sizes available for different breast sizes/types. The examination, lasting 8 min per breast, is performed with the woman lying face down.

**Figure 1 F1:**
[figure not shown]
MammoWave system and its operability. AI, artificial intelligence; eCRF, electronic case report form; RX, receiving; TX, transmitting.

MammoWave’s software employs an imaging algorithm based on Huygens’ principle (HP) to generate microwave images, which are intensity maps representing the homogeneity of breast tissues’ dielectric properties.^34 35^ Images are maximum intensity projection coronal two-dimensional (2D) maps of the entire breast volume. Specifically, after acquiring S_21_ data, the HP-based software produces microwave images and parameters describing them, such as the Max/Avg intensity ratio, used to assess images’ non-homogeneity. MammoWave’s output includes a label generated by a novel AI-based classification algorithm trained using previous clinical data (as described in the next subsection).

#### MammoWave’s AI-powered clinical decision support system

MammoWave’s novel software includes an AI (machine learning-based) classification algorithm. This algorithm has been developed using the clinical data collected in a previous international, multicentric study (ClinicalTrials.gov Identifier: NCT04253366). In particular, the labels (reference standard, ie, the output of conventional breast examination path) collected in such study were used for training and testing, with the aim of optimising the AI-based classification algorithm (to be used, prospectively, within this clinical trial).

This AI-based classification algorithm works on the S_21_ data of each scanned breast, which is a matrix of complex electromagnetic signals derived from the measurement performed for multiple positions of the TX and RX antennas and sampled in frequency. Principal component analysis methods were used to reduce the matrix’s dimensionality and fix the number of components so that at least 95% of the variance in the data is accounted for. Various algorithms were tested (support vector machines (SVM), decision trees, random forests, logistic regression, k-nearest neighbours), using the cross-validation methodology and calculating the performances in terms of specificity and sensitivity.^36^ More specifically, the SVM-based algorithm will be used within this trial to categorise breasts into two groups: WSF (breast With Suspicious Finding), indicating the presence of a suspicious lesion, or NSF (No Suspicious Finding), indicating the absence of a lesion or the presence of a low-suspicion lesion. More details related to algorithm’s validation methodology and performances in terms of specificity and sensitivity can be found in Papini *et al*,^36^ where specificity of up to ~90% and sensitivity of up to ~85% have been reported.

As an example, figure 2 shows MammoWave’s output and reference standard output is also shown.

**Figure 2 F2:**
[figure not shown]
(Left) Example of MammoWave output, which primarily consists of microwave image and includes the label generated by the novel AI-based classification algorithm, WSF for this breast; (Right) reference standard output and details are given for the same breast. AI, artificial intelligence; WSF, with suspicious finding.

### The clinical study

This study is entitled ‘A multicentric, prospective clinical investigation to evaluate microwave imaging via MammoWave in a population-based screening program for early breast cancer detection to make breast cancer screening more accurate, inclusive, and female-friendly’ and has been activated in March 2024 (ClinicalTrials.gov Identifier: NCT06291896).

#### Hypothesis and objectives

The aim of this clinical study is to validate, prospectively, MammoWave’s AI-based classification algorithm. The hypothesis underlying this clinical study is that MammoWave’s AI-based classification algorithm achieves a sensitivity of over 75% and a specificity of over 90% in the detection of BC within the screening process of asymptomatic individuals currently enrolled in population-based screening programmes.

The primary objective of this study is to generate evidence in the detection of BC by using MammoWave, evaluating its sensitivity and specificity, having as reference standard the output of conventional breast examination path (ie, screening mammogram, integrated with other radiological/histological output when deemed necessary by the responsible Investigator).

The secondary objectives of the study are as follows:

Evaluation of the sensitivity of MammoWave in detecting BC according to the American College of Radiology (ACR) BI-RADS classification.^37^Evaluation of the effectiveness of MammoWave versus a conventional reading of digital mammographic images (either 2D or tomosynthesis) and analysis of whether they are equivalent in terms of detection rates of BC (sensitivity),the number of recalls and positive predictive value (for the biopsies performed).Evaluation of the detection rate (sensitivity) of each system according to the type of mammographic radiological finding (microcalcification, mass, asymmetry or architectural distortion group).Evaluation of the impact of breast density (according to the ACR BI-RADS classification^37^ assigned by the radiologist, with or without automatic software if available) on the MammoWave detection rate of BC, number of recalls and positive predictive value (of the biopsies performed).Evaluation of the impact of breast density (according to BI-RADS classification assigned by the radiologist^37^) on the detection rate (sensitivity) of each system depending on the type of finding (microcalcification, mass, asymmetry or architectural distortion group).Comparison of radiological, histological and stage characteristics between the BCs detected by each system.Evaluation of the reproducibility of the AI-based MammoWave software’s results.Evaluation of the improvement in both sensitivity and specificity when retrospectively using AI algorithms to evaluate MammoWave data after its further optimisation with all the data collected in the patients included in the study.Volunteers’ satisfaction related to MammoWave use, through a properly designed questionnaire (given here as online supplemental material), collecting women’s issues during the exam with MammoWave in the language spoken by the women.

Additionally, there is a secondary objective, which is related to MammoWave safety and tolerability assessment. Furthermore, an additional exploratory objective of the clinical study is to establish a predictive model capable of discriminating and classifying lesions in MammoWave outcomes for volunteers with breast lesions, if feasible.

#### Study population, inclusion and exclusion criteria

The study will include consecutive volunteers who are participants of the local, regional or national BC screening programmes. These volunteers will fulfil all the prerequisites and inclusion criteria set forth by such programmes, following the European guidelines on BC screening and diagnosis^15^: asymptomatic women aged between 45 and 74 years, with no indications of BC suspicion and not currently enrolled in other clinical imaging pathways (such as pathological, high-risk or women with implants).

In more detail, participants fulfilling all the following inclusion criteria are eligible for the study: (1) women aged between 45 and 74 years old; (2) asymptomatic; (3) with signed informed consent form collected before starting any study activity; (4) with average risk of BC (every woman except those with known BRCA1, 2, TP53 and/or previous BC); (5) having a radiologist study output obtained using conventional mammographic exams, either 2D DM or 3D DBT (collecting oblique mediolateral projection (MLO) of the right breast, craniocaudal projection (CC) of the right breast, MLO projection of the left breast, CC projection of the left breast), performed within the past month with available results or planned to be performed in the same day of the MammoWave test or the subsequent days and (6) with a spontaneous willingness to comply with the clinical investigation plan (CIP) and recommendations.

The presence of any one of the following criteria will lead to the exclusion of the participant: (1) women with breast prostheses; (2) women with symptoms or some sign of suspected BC; (3) women with known BRCA 1, 2, TP53 or previous BC; (4) pregnant women; (5) women who do not have a mammographic manifestation of the tumour (known occult BC with only axillary manifestation) and (6) women with breast size larger than the largest MammoWave cup size.

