Following the study, a retrospective analysis will be conducted to refine an additional AI-generated algorithm using all acquired data. This algorithm will then be employed to re-evaluate the MammoWave data collected during the study, retrospectively reassessing the endpoints.

Regarding blinding strategies, the study will proceed as follows: first, each mammogram (either full-field DM or DBT) will be independently double-read by two radiologists, with consensus or arbitration for any discordant interpretations, in accordance with European breast screening guidelines (European Guidelines on Breast Cancer Screening and Diagnosis, ECIBC). Following this, all the eligible women will be enrolled consecutively, as detailed above. Blinding will be in place for the participants in the study. The output from MammoWave will be automatically transmitted to the responsible Investigator; blinding will be in place for MammoWave analysis.

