#### Choice of comparator/control intervention

MammoWave’s results (labels provided by its AI-based classification algorithm) will undergo validation against a reference standard, which represents the output of the conventional breast examination pathway. This pathway includes screening mammograms conducted with DM or DBT, integrated with other radiological/histological findings as required by the responsible investigator, following the site’s ongoing procedures and clinical circuit. The reference standard’s results will be categorised as ‘positive’ when BC presence is confirmed by histology (ie, BI-RADS 6), otherwise labelled as ‘negative’ (BI-RADS 1, 2 or 3). Specifically, within this study BI-RADS 4 and BI-RADS 5 are only image suspicion criteria: when a biopsy is performed, they will be categorised as ‘positive’ when BC presence is confirmed by histology (ie, BI-RADS 6), otherwise labelled as ‘negative’ (BI-RADS 1, 2 or 3).

Conventional mammogram studies (2D or tomosynthesis) will adhere to approved protocols and clinical practices for breast screening. Radiological reports and interpretations will align with international guidelines, particularly those set by the ACR.^37^ The radiologists involved in this study will have extensive experience in mammographic interpretation, serving as the benchmark during the study. Details such as single or double screening readings and the utilisation of AI-assisted mammographic reading will be documented at each centre. Additionally, the integration of conventional mammogram studies with other radiological/histological findings will occur when deemed necessary by responsible investigators, who will record relevant variables in the electronic case report form (eCRF) following their usual clinical practice.

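### The safeguard of reading every mammogram before enrolment cannot hold for women scanned with MammoWave first, so the label can be available before the reference reading is made

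*Protocol article*

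**What the plan says.** All references are to the protocol article.

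- **Order of events.** The paragraph on blinding in Study design says "first, each mammogram (either full-field DM or DBT) will be independently double-read by two radiologists, with consensus or arbitration for any discordant interpretations". It continues: "Following this, all the eligible women will be enrolled consecutively, as detailed above".
- **Eligibility.** Inclusion criterion 5 (Study population, inclusion and exclusion criteria) accepts a conventional mammogram from the previous month whose result is already known, or one "planned to be performed in the same day of the MammoWave test or the subsequent days". Study design also describes approaching women when they come for their scheduled mammogram, or when they had one in the past month.
- **Release of the label.** Study design describes real-time cloud processing of each scan. The blinding paragraph adds: "The output from MammoWave will be automatically transmitted to the responsible Investigator; blinding will be in place for MammoWave analysis". The strengths and limitations box says the system will "automatically provide radiologists with a dedicated label indicating the presence or absence of suspicious findings in each breast".
- **Who is blinded.** Blinding is named for participants, for the MammoWave analysis, and for the central reviewers at the end of the study, who do not see the reference standard.
- **Use of the output.** Study design bars the microwave images and their features from diagnostic decisions. It does not bar the label.
- **Who decides on work-up.** Hypothesis and objectives, and Choice of comparator/control intervention, leave further radiological or histological work-up to the responsible investigator, the role that receives the label.
- **Reading practice.** Choice of comparator/control intervention says: "Details such as single or double screening readings and the utilisation of AI-assisted mammographic reading will be documented at each centre".

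**The concern.** The reference reading is protected by sequence: if the mammogram is read and arbitrated before a woman is enrolled, no MammoWave label can exist to influence it. That protection disappears for any woman scanned before her mammogram is read, and criterion 5 permits this. Her label may be available while the mammogram is read or while further work-up is being decided.

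Two results are at stake. The secondary comparison of MammoWave with conventional reading (detection, recalls, positive predictive value) assumes that the mammographic result was formed without the label, so any leak contaminates it directly. Primary sensitivity is exposed less directly. A reference positive needs histology, so influence acts through who is recalled and biopsied. A not-suspicious label (NSF) can reassure, and a cancer missed for that reason leaves the denominator. A suspicious label (WSF) can prompt a recall that would not otherwise have happened. Both push apparent sensitivity upward, around a target of 75%.

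**Working it through.** **1. Do the sections agree?** The blinding paragraph requires mammogram, then double reading, then enrolment. Criterion 5 allows enrolment and MammoWave, then mammogram (same day or later), then reading. A woman on the second path cannot satisfy the first. Nor does the text present her as an exception, since women attending for a scheduled mammogram are one of the two recruitment routes in Study design.

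**2. Does another safeguard cover her?** Participant blinding does not reach the readers. Blinding of the MammoWave analysis, read naturally, keeps the index test from the reference and not the reverse. The central reviewers work after the study. Double reading that is independent makes the two readers independent of each other. None of these states that readers or the responsible investigator are kept from the label.

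**3. Inputs for size.** Prevalence 0.92%, target sensitivity 75%, 10 000 women and a minimum of 8000 (Number of participants).

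The plan's own figure first. Buderer's formula with a half-width of 0.10 gives 1.96² × 0.75 × 0.25 / 0.10² = 72.03 cancers, rounded up to 73. Then 72.03 / 0.0092 ≈ 7830 and 73 / 0.0092 ≈ 7935, both consistent with 8000.

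Expected cancers in 10 000 women: 10 000 × 0.0092 = 92. At 75% sensitivity, 69 are labelled WSF and 23 NSF.

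**4. NSF cancers lost from the reference.** If k are never confirmed, observed sensitivity is 69 / (92 − k). The values of k are assumptions.

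| k lost permanently | Estimate |
|---|---|
| 0 | 69/92 = 75.0% |
| 1 | 69/91 = 75.8% |
| 2 | 69/90 = 76.7% |
| 3 | 69/89 = 77.5% |
| 5 | 69/87 = 79.3% |

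**5. Effect of follow-up.** If 5 are missed at screening and follow-up recovers 3, then k = 2 and the estimate is 76.7%. If it recovers 4, then k = 1 and the estimate is 75.8%.

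**6. Effect of exposure.** Five of 23 is a 22% loss rate applied to all women. If half are scanned before reading (assumption), the same rate gives k = 2.5 and 69/89.5 = 77.1% before any recovery.

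**7. Extra WSF cancers.** If 5 further cancers are confirmed only because of the label (assumption), the estimate is (69 + 5) / (92 + 5) = 74/97 = 76.3%. Part of any such effect would arise anyway from the planned ultrasound after a WSF label.

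**The case against.** The strongest reply is that the text shows an opportunity for influence and no more. The label goes to the responsible investigator, who is not said to be a mammogram reader. The strengths and limitations box mentions radiologists but is a general description that says nothing about timing. A same-day mammogram may still be read first, and women who arrive with a result in hand are not exposed at all. The release rule may also be set out in the full investigation plan, which is not shown. All of this stands as a limit on size and certainty. It does not remove the conflict, because the article itself states the sequence as a blinding measure and then admits women for whom it cannot operate. The investigator who receives the label also decides on further work-up, whether or not that person reads mammograms.

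A second reply is that the 2-year follow-up recovers missed cancers. It may recover some. However, the first evaluation is planned for December 2026 while recruitment runs to February 2026, so women enrolled after December 2024 will not have completed two years by then. The Follow-up section describes checking whether interval cancers had been called positive by MammoWave; it does not mention those labelled NSF. Follow-up also cannot restore a mammographic reading made with knowledge of the label.

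A third reply is that WSF labels trigger ultrasound by design. That is correct: it is a separate, openly planned influence, and this point does not depend on it.

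A reader might also infer that some centres will read singly, or that AI-assisted reading breaks the double-reading rule. The text supports neither. It says reading practice will be documented, and AI assistance is compatible with two readers. The real tension is narrower: one section has every mammogram double-read, while another provides for recording single or double reading.

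**Conclusion.** The contradiction between the blinding paragraph and inclusion criterion 5 is certain on the text. That the label can precede the reading for some women follows from it. That readers will see the label, or be swayed by it, is possible and not shown.

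A reader might take 79.3% as the expected bias. The documents do not support that. It is the top of an illustrative range that assumes five of 23 NSF cancers are lost, exposure among all women, and no recovery in follow-up. The supportable statement is an upward shift from 75.0% to somewhere between 75.8% and 79.3% if 1 to 5 NSF cancers are permanently lost out of 92, and smaller to the extent that follow-up recovers them. The share of women scanned before reading is not given, so the actual size cannot be fixed. The comparison with conventional reading is the result most directly affected. The point should be acted on because it is cheap to close and the primary target is a fixed threshold close to these values.

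**What to change.** - **Release gate.** Have the platform withhold the label from investigators and readers until the final mammographic BI-RADS for both breasts, after any second reading and arbitration, is entered and locked in the eCRF. Then release it, so that the planned pathway after a WSF label is otherwise unchanged.
- **Sensitivity analysis.** The eCRF already records the date and time of entries. Use these times to repeat the primary analysis and the mammography comparison without women whose label was available before the reading was locked. This also covers women already enrolled.
- **Wording.** Reconcile criterion 5 with the sequence in the blinding paragraph, and state who is kept from the label and until when. Reconcile universal double reading with the provision for recording single or double reading by centre.

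The cost is a change to the platform and eCRF plus an edit to the text. The downside is that the label arrives later for women scanned before their mammogram is read. The gate does not remove the separate influence of the planned ultrasound after a WSF label, which should be acknowledged when sensitivity is reported.
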